### Recruitment

Mother-daughter dyads will be recruited across 40 counties in east Tennessee using two primary strategies: (1) Coordinated School Health (CSH) Coordinators in each school system will provide access to mothers and daughters in high schools, and (2) study staff will recruit mothers and daughters through partnerships with community-based organizations (eg, churches, sports leagues, clubs, health clinics, etc). A local Expert Advisory Board, made up of regional CSH Coordinators, public health educators, and maternal and child health professionals is providing insight into effective community-based recruitment. CSH, which is housed in the Tennessee Department of Education, has the mission of working with schools and parents to improve children’s health, making them a natural partner in this effort. CSH Coordinators are asked to send study invitations to mothers through their normal channels (eg, back-to-school packets, flyers with report cards, email, newsletters, etc). Access to families through schools can be challenging, but partnering with CSH ensures we will not interfere with time, curricular, and other constraints. Schools that assist with mother-daughter recruitment will receive a US $200 mini-grant for CSH-related program materials. At the same time, study staff will systematically canvass communities across the region, beginning in the far northeast corner of the state and working their way south and west to partner with local organizations, media outlets, and employers to advertise the study to mothers and teen daughters in the region. We chose multiple recruitment methods based on our past experience recruiting women and adolescent girls in this hard-to-reach population [46]. CSH Coordinators and community-based organizations often have direct access to mothers of high school students and can serve as credible recruiters. For eligible participants, we expect a refusal rate of 30%, based on our previous experiences in this population [46].

Mothers are the target of recruitment efforts and must enroll in the trial first and then provide permission for their daughters to participate along with their daughters’ contact information. Interested mothers will sign up for the trial by visiting a study website where information is provided along with a screener that asks if they have a daughter ages 14-17 in the home, if they are a Tennessee resident, and if they have or are willing to have a Facebook account. Eligible mothers are sent to the consent and baseline survey.

When a mother completes the baseline survey, the enrollment website will send invitations to the daughter to assent and complete her own baseline survey. These invitations will be sent by email with up to 5 weekly reminders. Mothers remain eligible and enrolled in the study even if daughters do not provide assent; in such cases, daughters’ missing responses will be imputed.

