**Methods:**

The study is a 12-month randomized controlled trial comparing 2 conditions: an attention control Facebook private group where content will be relevant to teen health with 25% focused on prescription drug abuse, a topic unrelated to tanning; and the intervention condition will enter participants into a Facebook private group where 25% of the teen health content will be focused on indoor tanning. A cohort of 2000 mother-teen daughter dyads will be recruited to participate in this study. Only mothers will participate in the Facebook groups. Both mothers and daughters will complete measures at baseline, end of intervention (1-year) and 6 months post-intervention. Primary outcomes include mothers’ permissiveness regarding their teenage daughters’ use of indoor tanning, teenage daughters’ perception of their mothers’ permissiveness, and indoor tanning by both mothers and daughters.

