We used the Optimal Design software package (version 3.0) [45] to determine sample size. Assuming a 2-tailed alpha of 0.05, a moderate effect size of d=0.50, and an intraclass correlation of 0.05 within each Facebook private group, we far exceed a power of 0.80 with 50 Facebook private groups each consisting of 25 mothers (total n=1250 mothers and 1250 daughters). We increased this sample size to account for the proportion of minority mothers and daughters (15%) we expect to recruit to achieve the needed sample size of non-Hispanic whites, the racial/ethnic group most likely to indoor tan and with the highest rates of melanoma [40]. We further inflated the sample to account for an expected loss to follow-up of 30% by 12 months (20% at 6 months). Thus, we will recruit initial samples of 2100 mothers and 2100 daughters (42/Facebook group) at baseline and expect to successfully assess 1680 in each sample (approximately 34/Facebook group) at the 6-month follow-up and 1470 in each sample (approximately 29/Facebook group) at the 12-month follow-up, with the final samples containing 1250 non-Hispanic white mothers and 1250 non-Hispanic white daughters for analysis.

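### The recruitment target is 2000 dyads in two places and 2100 in the power section, and the 1250 daughters planned for analysis allow for no daughter declining assent

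*Protocol article*

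**What the plan says.** On the target, the Abstract (Methods) and the Participants section carry the same sentence: "A cohort of 2000 mother-teen daughter dyads will be recruited to participate in this study". The Sample Size and Power Calculations section says instead that "we will recruit initial samples of 2100 mothers and 2100 daughters (42/Facebook group) at baseline". The Study Design section describes 25 waves of about 84, giving 50 groups of about 42.

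On the final number, the power section expects "final samples containing 1250 non-Hispanic white mothers and 1250 non-Hispanic white daughters for analysis". It reaches this with two inflation factors only, a 15% minority share and 30% loss by 12 months, applied identically to mothers and daughters.

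On assent, the Participants section makes it an eligibility criterion for daughters. The Recruitment section has the mother enrol first, after which the daughter is invited by email with reminders. Mothers stay in the trial even if "daughters do not provide assent; in such cases, daughters’ missing responses will be imputed".

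**The concern.** There are two separate problems with one number.

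First, the article gives two recruitment targets, and they are not interchangeable: only one produces the final sample that the power section states. A team that stops at 2000 will have met the target in the Abstract and missed the one behind the calculation.

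Second, daughters can enter only through an enrolled mother. The plan foresees that some will not assent, but the daughter column of the sample size has no allowance for this. Daughters' perception of permissiveness and daughters' own tanning are both named in the primary hypothesis. A daughter who never assents has no data at any visit, so an imputed value for her adds no independent information on either outcome. The number of daughters who inform these outcomes is then smaller than a reader of the power section would believe.

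**Working it through.** **Inputs.** From Sample Size and Power Calculations: 1250 per sample required for analysis, 15% minority share, 30% loss by 12 months and 20% at 6 months, 50 groups, "Assuming a 2-tailed alpha of 0.05, a moderate effect size of d=0.50" and "an intraclass correlation of 0.05 within each Facebook private group". From Study Design: 25 waves of about 84, and 50 groups of about 42. From the Abstract and Participants: 2000 dyads. The assent rate is not given, so the values used in step 4 are assumptions.

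**1. Reproduce the plan's figure.** Required recruitment = 1250 / (0.70 × 0.85) = 2100.8, against 2100 stated. Forward: 2100 × 0.80 = 1680; 2100 × 0.70 = 1470; 1470 × 0.85 = 1249.5. Every step matches the power section.

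**2. Check the design against it.** 25 × 84 = 2100 and 50 × 42 = 2100. Study Design supports 2100.

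**3. Put 2000 through the same chain.** 2000 × 0.70 = 1400; 1400 × 0.85 = 1190. The shortfall is 1250 − 1190 = 60, or 60/1250 = 4.8%, with every daughter assenting. The 14% minority share quoted in Participants does not rescue it: 1400 × 0.86 = 1204.

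**4. Add assent.** Observed non-Hispanic white daughters = 2100 × a × 0.70 × 0.85, where a is the proportion of enrolled mothers whose daughter assents. This assumes that loss and ethnic mix are the same among assenting daughters. Each percentage point of non-assent removes 2100 × 0.01 × 0.595 ≈ 12.5 daughters.

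**5. Consequence for power.** With J = 50 groups of m and intraclass correlation 0.05, SE(d) = √[4(0.05 + 0.95/m)/50]. Power uses a noncentral t on 48 df. The detectable d at 80% power is (1.96 + 0.84) × SE. For m = 25, SE = √(0.08 × 0.088) = 0.0839, so the detectable d is 0.235.

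| Assent (assumed) | Observed daughters from 2100 mothers | Per group | Power at d=0.50 | Detectable d |
|---|---|---|---|---|
| 100% | 1250 | 25.0 | >0.9999 | 0.235 |
| 90% | 1125 | 22.5 | 0.9999 | 0.241 |
| 80% | 1000 | 20.0 | 0.9998 | 0.247 |
| 70% | 875 | 17.5 | 0.9997 | 0.256 |
| 50% | 625 | 12.5 | 0.998 | 0.281 |

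For a target of 2000 with full assent (1190, or 23.8 per group), power is 0.9999 and the detectable d is 0.238.

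**The case against.** The strongest reply is that this is bookkeeping. The inflation chain reproduces, 2000 may be a rounded figure, and the plan itself says that "we far exceed a power of 0.80 with 50 Facebook private groups each consisting of 25 mothers (total n=1250 mothers and 1250 daughters"). On power that reply stands: none of the shortfalls above threatens 0.80 at d=0.50. It does not remove the contradiction, because the power section names 1250 as the number for analysis and 2000 does not reach it.

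A reader might also infer four stronger things that the article does not support.

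- *That imputed daughters are counted within the 1250.* No section says so. The power section speaks of daughters the team expects to assess successfully, and full assent may simply have been assumed.
- *That a particular share of daughters will not assent.* The one refusal figure ("we expect a refusal rate of 30" per cent) concerns eligible participants and is not described as daughters' non-assent after the mother has enrolled. The daughter numbers above are illustrations.
- *That standard errors will be too small.* That follows only if imputed values are analysed as though observed. The article says only that responses will be imputed; proper multiple imputation would not have this fault, and the method may sit in an analysis plan that is not shown.
- *That replacing imputation by a likelihood analysis would cure bias.* Full-information likelihood and multiple imputation on the same variables rest on the same missing-at-random assumption. If assent depends on tanning in ways the data do not capture, neither removes the problem.

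**Conclusion.** The point holds in a limited form. The conflict between 2000 and 2100 is a plain contradiction that needs no assumption: 2100 delivers 1250 and 2000 delivers 1190, which is 4.8% short. The daughter sample is overstated to the extent that assent falls below 100%. The direction is certain once any daughter declines, but the size is unknown because no assent rate is stated; over an assumed 90% to 70% it is about 1125 to 875 observed daughters.

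The trial is not underpowered at its own effect size: power stays above 0.99 even at 50% assent, and the detectable d moves from 0.235 to 0.281. The power figures rest on the plan's 50 groups, its intraclass correlation of 0.05 and equal group sizes. What needs correcting is the stated target, the stated number of daughters, and the disagreement between assent as a criterion in Participants, equal samples in the power section, and imputation in Recruitment.

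**What to change.** - Replace 2000 with 2100 in the Abstract and in Participants, so that all sections match the power section and Study Design.
- State an expected assent rate in the power section and restate the number of daughters who will actually be observed. Power leaves room for this without enrolling more dyads.
- Reconcile Participants, Recruitment and the power section so that daughters who never assent are not counted as assessed.
- Report the daughter outcomes on assenting daughters within the planned dyadic multilevel model, keeping all mothers. Present any imputation for never-assenting daughters as a sensitivity analysis.

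The cost is wording in four sections and a stated daughter sample that looks slightly less favourable.

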### Intervention

#### Conceptual Framework

The intervention, named *Health Chat*, will be delivered in a private Facebook group. It was designed using an integrated conceptual framework combining 3 complementary theories of social and individual change to guide the intervention social media posts and attempts to generate user engagement in the Facebook groups. Content of the social media posts from the social media intervention were designed based on principles of social cognitive theory (SCT) [47,48] and transportation theory (TT) [49,50]. From SCT, the posts were written to address the social situation (increasing perceived social norms to not indoor tan or give permission for daughter to tan), behavioral capability (knowledge of the risks of indoor tanning and skills to refuse indoor tanning requests and invitations), expectations (belief that indoor tanning increases risk for melanoma), observational learning (in stories from real mom’s about the dangers of letting their daughters indoor tan, including about daughters who developed melanoma as young adults), self-efficacy to avoid indoor tanning (suggestions for how to have daughter refuse indoor tanning invitations), and interest in alternatives to indoor tanning (such as using sunless tanners or going with friends for spa treatments rather than indoor tanning). A key tenet was that the intervention needs to provide parents skills for communicating with their teens (ie, active listening, self-disclosure, showing empathy, and managing conflict), not just information on the risks of indoor tanning. From TT, a number of intervention posts contained links to news stories or stories provided by public health organizations from mothers and daughters about the risks of indoor tanning and their wish they had not given permission to indoor tan or avoided indoor tanning. These stories should be very effective at influencing individuals to alter their behaviors [51] because (1) people transported into a narrative world will alter their beliefs based on information, claims, or events depicted [52], (2) individuals identify with characters in a story, and identification increases the likelihood of social influence [53,54], and (3) narratives shift normative beliefs about risks [55-62]. To test our theoretical framework, all intervention messages are classified in 3 ways: (1) narrative versus didactic, (2) social norms–based versus not, and (3) appearance- versus health risk–based. Secondary analysis will probe which type of messages drive the most engagement among participants.

TT and diffusion of innovations theory (DIT) [63] were used to explain importance of soliciting user engagement from the mothers in the social media intervention, in the form of comments, shares, and likes. These theories guided our plan to encourage user-generated content and discussion on Facebook to capitalize on the interpersonal and interpretive processes in social networks that can produce sustained changes in health beliefs and behaviors. For instance, in social media, user-generated content such as testimonials and comments from other mothers, especially those phrased as stories, may be more powerful than conventional persuasive messages in posts alone, according to TT [51]. Likewise, DIT [63] explains how comments, shares, and likes from users in the social media should increase dissemination and impact of the intervention posts. It holds that social influence occurs through a process of delivering both carefully crafted messages and diffusion of these messages by community members, especially opinion leaders. The intervention will continually invite mothers to provide comments, shares, and likes in the hopes that opinion leaders will emerge in each of the Facebook groups. These opinion leaders should stimulate collective action among the mothers because people depend on them for information, especially about issues that carry risk and produce uncertainty [64-66], which opinion leaders deliver through their central position in a social group and links to outside information sources [63]. The information shared among mothers in the Facebook groups should breed collective action, as mothers interpret and respond to it through social comparison [63,67-69]. Mothers are expected to routinely compare themselves with other social network members [70] and conform with these peers to avoid uncertainty that arises when attitudes and behavior deviate [71]. In the process, they perceive themselves in abstract social categories and roles (eg, female, friend, mother, white, healthy person), which become part of their collective identity in the group, stabilizing behavior changes [67,68]. User engagement will be assessed in the form of number of posts, comments, likes, and views in the *Health Chat* program to test its influence on intervention outcomes.

#### Content

All participants will be invited to private Facebook groups to participate in the *Health Chat* program. The privacy setting in these groups is set to “secret” to prevent members and content of the group being visible to the public, including other Facebook users. Members of a private group with a “secret” privacy setting can only see information in each other’s profiles as indicated by their personal privacy settings. Members must also be invited to the group by the group administrator who will be a study staff member. The content of *Health Chat* is tailored to mothers and although only mothers will be in the Facebook groups, they will be encouraged to share content with their daughters. Posts will occur twice daily for 12 months for a total of 720 posts. Mothers will be encouraged to contribute their own content to the Facebook group via comments, original posts to share opinions or pose questions, and participation in group activities. Each group will be hosted by a community manager who will oversee the editorial calendar, maintain the feed, stimulate engagement, and monitor the broader media environment to discover trending topics and new research findings to post.

Our preliminary focus groups of mothers and key informant interviews of CSH coordinators revealed greater interest in a Facebook group focused broadly on health as opposed to a single topic like indoor tanning. For this reason, the *Health Chat* program will address health topics identified as of high interest by our focus group participants and CSH coordinators. These topics include healthy lifestyle, mental health, mother-daughter communication, and substance use. An advisory board of experts on these health topics provided evidence-based protocols and resources, which were then converted to Facebook posts by our team. In the *Health Chat* feed, 80% of posts were developed in advance based on evidence-based interventions and resources while 20% of posts will be pulled from emerging research and current events (eg, news reports of new tanning legislation, public service announcements about the health topic) relevant to the health topics.

#### Indoor Tanning Content

Indoor tanning content was developed by the investigators and a social media marketing expert using information from published literature on risk factors, evidence-based intervention content from published trials targeting indoor tanning [43,46,72-75], public health campaigns from major nonprofit organizations (eg, CDC, Skin Cancer Foundation, etc), and investigator-developed, video-recorded interviews of local mothers and professionals about the risks of indoor tanning, experiences with skin cancer, and mother-daughter communication role modeling.

Facebook posts on indoor tanning are intended to achieve the following: (1) increase awareness of state policy on indoor tanning by minors and teen interest in indoor tanning, (2) improve knowledge of indoor tanning risks, including skin damage (wrinkling/aging) and cancer, (3) teach mothers skills and improve self-efficacy for resisting daughters’ requests to indoor tan (eg, starting conversations, addressing sensitive topics, and managing conflict), (4) convey the importance of modeling tanning avoidance to daughters, (5) increase understanding of the reasons why adolescent girls indoor tan (eg, for stress reduction, self-medication of seasonal affect disorder, peer pressure, etc), (6) highlight behavioral alternatives to indoor tanning for adolescents (eg, sunless tanning, yoga, exercise, manicures/pedicures, and other spa treatments that enhance appearance, body image, and stress coping skills), (7) promote behavioral alternatives [72], and (8) give advice to avoid sun tanning and practice sun protection (ie, wear protective clothing, hat, and eyewear; seek shade; avoid midday sun; apply/reapply sunscreen with SPF 15+) grounded in SCT. Each message was designed according to our theoretical framework to ensure messages are balanced across (1) didactic versus narrative, (2) social norms based versus not, and (3) appearance- versus health risk-based messages. Once messages were developed, the entire investigative team reviewed the messages and made edits according to consensus. To evaluate the acceptability and readability of messages, focus groups were conducted with mothers of teenage daughters who viewed the messages in a private Facebook group for 1 week. Focus group participants rated each message on clarity, aesthetics, negative versus positive valence, interest, credibility, similarity to typical social media posts, and likelihood they “like,” comment, or share the post. Messages were then refined based on feedback.

### Control Condition

The East Tennessee State University Center for Prescription Drug Abuse/Misuse was consulted for content on opiate drug abuse. Relevant content from their website, as well as the Tennessee State Government [76], Kids Health [77], and National Institute on Drug Abuse for Teens websites [78], were converted into intervention posts.

### Measures

The primary outcomes are mothers’ permissiveness for daughters’ indoor tanning, mother and daughter indoor tanning behavior, and mothers’ support for stricter bans on indoor tannings in minors. Engagement with the *Health Chat* program and potential moderators and mediators of campaign effectiveness will also be assessed.

#### Primary Outcomes

Mothers’ permissiveness for daughters to tan indoors will be assessed using 4 Likert-type items (1=strongly disagree, 5=strongly agree) assessing permissiveness toward their teenage daughters’ indoor tanning [79]. Example items include, “I would allow my daughter to indoor tan,” and “I think it’s OK for my daughter to indoor tan” (Cronbach alpha=.97). Daughters will be asked the same 4 items to assess their perceptions of mothers’ permissiveness (Cronbach alpha=.95) [46]. Maternal permissiveness will be assessed at baseline and both follow-ups by the combined average ratings across the 6 items.

Indoor tanning behavior will be assessed by asking mothers and daughters to report on their indoor tanning over the last year using a single open-ended item (ie, “How many times in the past year have you used a tanning bed or booth?”) [80] Similar measures had strong positive correlations with diary measures of indoor tanning behavior (*r*=.77-.86, *P*<.001) in previous work [81,82]. Intention to indoor tan will also be assessed (ie, How likely is it that you will indoor tan in the next 3/6/12 months; 7-point Likert response scale), along with intention to get a sunless tan (eg, self-tanners, spray tans) in the next 12 months. We also will include an item specific to the months of December-March to capture indoor tanning during the seasonally high months of indoor tanning use. Indoor tanning behavior and intentions will be assessed at baseline and both follow-ups.

Support for strengthening bans on indoor tanning by minors will be measured via the Web server, which will record whether mothers who click on the link to “sign” the petition to strengthen the ban on indoor tanning and forward it to their legislator. At the final follow-up, mothers will be asked how much they support bans on indoor tanning by minors and about their reasons for either signing or not signing the petition.

